## Abstract

**Background:**

Knee osteoarthritis (OA) is characterized by chronic pain, physical dysfunction, and reduced quality of life. Low-load resistance exercises with blood flow restriction (BFR) have presented results similar to those of high-intensity resistance exercise (HIRE) without BFR provided that the exercise volume in both is paired. However, it is unclear whether BFR exercise with reduced load and volume generates clinical improvements similar to those of HIRE. The aim of the proposed study is to evaluate the effects of BFR resistance exercise with very low load and low volume against HIRE in patients with knee OA for the outcomes of knee pain, muscle performance, physical function, disease severity, quality of life, perceived exertion during the exercises, adherence, and patient satisfaction with treatment.

**Methods:**

This two-arm, prospectively registered, randomized controlled trial with blinded assessors and volunteers will involve 40 patients with knee OA. Two weekly treatment sessions will be provided for 12 weeks. Patients will perform very low-load (10% of 1-RM) and low-volume BFR exercise or HIRE (60% of 1-RM) for strengthening thigh muscles. The primary outcome will be the knee pain measured after 12 weeks of treatment. The secondary outcomes include knee pain 6 months after randomization, physical function, disease severity, quality of life, muscle performance, knee pain and perceived exertion during exercise, adherence, and patient satisfaction with treatment.

**Discussion:**

If the improvements in the outcomes are similar in the two groups, BFR exercise with reduced load and volume may be an interesting alternative in the treatment of knee OA, especially when exercises with high loads generate joint pain.

**Trial registration:**

*Registro Brasileiro de Ensaios Clínicos* (REBEC), RBR-6pcrfm. Registered on July 10, 2018.

**Electronic supplementary material:**

The online version of this article (10.1186/s13063-019-3238-2) contains supplementary material, which is available to authorized users.

## Background

Osteoarthritis (OA) is the most common type of arthritis and is characterized by inflammation and major structural changes in the joint [1, 2]. This condition is debilitating because of pain and physical disability, leading to a significant reduction in quality of life [3]. The knee joint is strongly affected by OA, and the weakness of the quadriceps muscle is a major risk factor for knee OA [4].

Strengthening knee extensor muscles is recommended as a key point in reducing pain and disability in these patients [5], and resistance exercises with loads greater than 60% of 1 maximal repetition (1-RM) are classically prescribed to gain strength [6, 7]. However, movements with high loads in the knee with OA can aggravate pain, swelling, and inflammation [8] and consequently reduce adherence to exercise [9]. Resistance exercise with blood flow restriction (BFR) has recently been considered in the treatment of knee OA [10, 11]. BFR resistance exercise is usually performed with lower load (20–30% of 1-RM) combined with a pneumatic cuff inflation that reduces arterial flow and limits the venous return, thus elevating metabolic stimulus in working muscles [12].

BFR exercise may be useful in knee OA treatment because of the possibility of strength gains associated with lower levels of pain, perceived exertion, overload, and joint stress during the training sessions compared with high-intensity (≥60% of 1-RM) resistance exercise (HIRE) without BFR [13–16]. However, it is unclear whether BRF is really required, even in resistance exercises with loads less than 30% of 1-RM [8, 17]. In subjects with knee OA, 8 weeks of resistance training with high (60% of 1-RM) or very low (10% of 1-RM) load without BFR induced similar improvement in pain and muscle function, as the total exercise volume (series × repetitions × load) was paired [8]. In addition, regardless of the load (20% or 50% of 1-RM), exercise volume, or BFR, healthy and untrained individuals presented similar strength increases after 8 weeks of resistance training in which the repetitions were performed until failure [17].

Importantly, in most studies on BFR exercise for knee pain, despite the low load (20–30% of 1-RM), the total volume is very close to [18, 19] or greater than [15, 20] the HIRE volume (~60% of 1-RM) because of a greater number of repetitions in BFR exercise. Thus, it is unclear whether the strength gains promoted by BFR exercise in subjects with knee OA are due to the additional metabolic stimulus promoted by BFR or only to the similar volume when compared with HIRE.

Therefore, this study aims to evaluate the effects of BFR resistance exercise with very low load and low volume against HIRE in patients with knee OA for the outcomes of knee pain, muscular performance, physical function, and quality of life. An additional objective is to identify which exercise protocol will induce lower levels of knee pain and perceived exertion during the exercises and greater adherence and patient satisfaction with treatment.

## Methods

### Study design

This is a prospectively registered, two-arm randomized placebo-controlled trial with concealed allocation, blinded measurers and volunteers, intention-to-treat analysis, and 3 months of follow-up (Fig. 1). Subjects with knee OA will be recruited via online media advertisement, personal invitation, telephone, and SMS. Volunteers will be randomly allocated to the BFR exercise group or HIRE group, and the outcome measures will be evaluated in the time points shown in Table 1.

**Fig. 1 Fig1:**
[figure not shown]
Flow diagram of the planned protocol pathway. Abbreviations: *BFR* blood flow restriction; *HIRE* high-intensity resistance exercise. *During the exercise sessions, the outcomes knee pain, perceived effort, and feelings of pleasure/displeasure will be measured (Feeling Scale)

**Table 1 Tab1:** Time point of outcomes

Outcome measures	Time points														
	Baseline	Weeks of treatment													Follow-up
	W0	W1	W2	W3	W4	W5	W6	W7	W8	W9	W10	W11	W12	MPT	W24
VAS	√													√	√
Lequesne	√													√	√
SF-36	√													√	√
TRP	√			√			√			√				√	√
Functional tests	√													√	√
Isometric and isokinetic tests	√													√	√
7–10 RM test	√			√			√			√				√	√
VAS during exercise		√	√	√	√	√	√	√	√	√	√	√			
Borg		√	√	√	√	√	√	√	√	√	√	√	√		
Feeling Scale		√	√	√	√	√	√	√	√	√	√	√	√		
GPE														√	√

*Abbreviations:*
*GPE* Global perceived effect, *MPT* Measures 72 h post treatment, *TRP* Total restriction pressure, *VAS* Visual analog scale, *W* Week

Analyses of inclusion criteria, getting informed consent, data collection, and statistical analyses will be carried out by researchers blinded to group allocation. Participants will receive oral and written instructions about study risks and benefits and sign a consent form. All personal data will be confidential. The study has obtained ethical approval from the Research Ethical Committee of Universidade Federal do Rio Grande do Norte (CAAE: 91753618.4.0000.5537). The trial was prospectively registered at the *Registro Brasileiro de Ensaios Clínicos* (*RBR-6pcrfm*). All participants will sign an informed consent form prior to participation. The study follows the SPIRIT (Standard Protocol Items: Recommendations for International Trials) 2013 checklist [21] (Fig. 2 and Additionalfile 1) and the TIDieR (Template for Intervention Description and Replication) [22].

**Fig. 2 Fig2:**
[figure not shown]
Study design schedule in accordance with the Standard Protocol Items: Recommendations for Interventional Trials (SPIRIT) checklist. Abbreviations: *BFR* blood flow restriction, *HIRE* high-intensity resistance exercise

### Inclusion and exclusion criteria

A total of 40 men and women with unilateral or bilateral knee OA diagnosed according to the American College of Rheumatology criteria will be considered eligible if they:are at least 50 years of age;are in the postmenopausal period (for women);are between 1.50 and 1.75 m in height;have a body mass index between 18.5 and 35 kg/m^2^;have moderate to very severe knee OA (score between 5 and 13 on the Lequesne Questionnaire);have a score of at least 24 on the Mini-Mental State Examination;do not have peripheral vascular disease, systolic blood pressure greater than 160 or less than 100 mm Hg, diastolic blood pressure greater than 100 mm Hg, deep vein thrombosis, diabetes, history of myocardial infarction, stroke in the previous year, or history of cancer that has generated limitations to exercise;do not have other orthopedic/neurological diseases that affect gait and do not present any other inflammatory myoarticular disease;have not undergone surgery or any invasive procedure on the knees in the previous 6 months;have not participated in physiotherapeutic treatment or lower-limb strengthening programs in the past 3 months;are not practicing regular physical activity (two or more times per week) for lower limbs (except for those who only practice walking).

Participants will be excluded if they:experience pain that completely prevents them from performing the exercises proposed by two consecutive or three non-consecutive sessions or refuse to remain in the study;begin taking specific medications that are for OA or that interfere with study outcomes;begin to exercise or perform other treatment modalities for knee OA after initiating treatment.

Patients will be able to maintain treatment with stable doses of anti-inflammatory or other medications of regular use in the 3 months prior to the start of the study [15, 23] but should avoid using medications on evaluation days. Subjects who discontinue participation in the study will be invited to participate in the assessments 3 months after the start of treatment, and 6 months after the randomization. Thus, all individuals will be included in the intention-to-treat analysis. Therapists who deliver the intervention will be eligible if they have undergone specific training for the treatment protocol.

### Randomization

Volunteers included will be randomly allocated to BFR exercise or HIRE groups by using the website www.randomization.com. Balanced permutations in blocks with respect to the presence of unilateral or bilateral knee OA will be used. Participant allocation will be concealed in sequentially numbered and sealed opaque envelopes prepared prior to the study by a research assistant, who will not be involved in the study.

### Intervention

The intervention will consist of two weekly sessions with about 60 min of duration each during 12 weeks for a total of 24 sessions. The volunteers will be re-evaluated after 12 weeks and from then on will be guided to practice exercises according to their own volition [20]. In both groups, the sessions will be started with 5 min of light-intensity warm-up on a stationary bike. All subjects included will be instructed not to initiate regular exercises beyond treatment sessions [8, 18]. Both groups will perform bilateral strengthening of the thigh muscles through squatting exercises on the hack machine (angle between 0° and 60° of knee flexion) and leg extension exercises (angle between 90° and 45° of knee flexion) [11, 20]. These amplitudes of movement were selected to minimize the load of the patellofemoral joint during the exercises [24].

In addition to exercises to strengthen the thigh muscles, trunk, hip, and calf exercises will be performed for both groups. High- or low-intensity exercises for strengthening thigh muscles are strongly recommended [25]. Although other studies have focused only on strengthening thigh muscles [8, 11, 18, 20], we chose an overall treatment because of the pathophysiology of knee OA [26] and because there is strong evidence that associating knee exercise and training of proximal and distal muscles to this joint is effective in patients with knee pain [27, 28]. The detailed exercise protocol is shown in Table 2.

**Table 2 Tab2:** Treatment protocol performed by the high-intensity resistance exercise group and blood flow restriction exercise group (adapted from Bryk et al. [15], 2016)

High-intensity resistance exercise group	
- Hamstring stretching, three repetitions of 30 s	
- Bridge with isometric contraction of the transversus abdominis, CORE training, three repetitions of 30 s ^+^	
- Hip abduction with weights (lying on side), three sets of 10 repetitions ^+^	
- Calm exercises (lying on side) with elastic band, three sets of 10 repetitions ^+^	
- Calf raises, three sets of 10 repetitions ^+^	
- Sensori-motor training (standing) on a mini-trampoline, three repetitions of 30 s	
- Squats on a hack machine, 0°–60° of knee flexion, three sets of eight repetitions *	
- Seated knee extensions (machine), 90°–45° of knee flexion, three sets of eight repetitions *	
Blood flow restriction exercise group	
- Hamstring stretching, three repetitions of 30 s	
- Bridge with isometric contraction of the transversus abdominis, CORE training, three repetitions of 30 s ^+^	
- Hip abduction with weights (lying on side), three sets of 10 repetitions ^+^	
- Calm exercises (lying on side) with elastic band, three sets of 10 repetitions ^+^	
- Calf raises, three sets of 10 repetitions ^+^	
- Sensori-motor training (standing) on a mini-trampoline, three repetitions of 30 s	
- Squats on a hack machine, 0°–60° of knee flexion, one set of 30 repetitions and three sets of 15 repetitions ^‡^	
- Seated knee extensions (machine), 90°–45° of knee flexion, one set of 30 repetitions and three sets of 15 repetitions ^‡^	

The interval between sets will be 30 s and between exercises will be 2 min

*Load is 60% of the 1-repetition maximum

^+^The load will be adjusted every 3 weeks to maintain an effort perception between 6 and 7 on the Borg scale

^‡^Load is 10% of the 1-repetition maximum

Loads of 10% and 60% 1-RM in the BFR exercise and HIRE groups, respectively, will be estimated (1-RM estimated) from the maximum load that can be overcome in 7–10 repetitions (7–10 RM test) [20] based on the Brzycki equation, (W/(1.0278–0.0278 × R), where W refers to weight used in the repetitions until failure and R refers to repetitions to failure [29, 30]. The load will be readjusted every 3 weeks with a 2- to 4-day interval after the last treatment session to prevent residual exercise fatigue from interfering with the 7–10 RM test. Five minutes of warm-up will be performed on a stationary bike before the 7–10 RM test [20, 31]. In relation to the 1-RM test, the 7–10 RM test has the advantage of minimizing the effect of pain on maximum force generation [20].

Participants will be advised that knee pain or discomfort during exercise is normal and that this does not necessarily cause joint damage [9]. All exercises should be performed with pain levels between 0 and 5 on the visual analog scale (VAS) defined as acceptable pain. The session will be interrupted if the patient reports pain greater than 5 or is unable to complete the exercise [23]. The load will be reduced by 20% (relative to 60% of estimated 1-RM) in the HIRE group if the pain prevents the volunteers from completing the exercise [20].

#### Blood flow restriction exercise

The BFR exercise group will perform the squatting on the hack machine and leg extension combined with a BFR corresponding to 60% of total restriction pressure (TRP) in both thighs [20]. The TRP will be individually determined to generate similar metabolic stimulus between participants [32]. After 10 minutes of rest in a climatized room (between 23° and 25 °C), the TRP will be determined with volunteers positioned in supine decubitus with their upper and lower limbs relaxed. The transducer (5 to 10 MHZ) of a portable vascular Doppler (DV 2001, MEDPEJ, Ribeirão Preto, Brazil) will be positioned at the ankle at a mean distance between medial malleolus and calcaneus tendon to capture the auscultatory signal of the posterior tibial artery. A manufactured pneumatic cuff (10 cm width and 80 cm length) will be positioned on the proximal end of the thigh [31, 33] and inflated based on a previous protocol [34]. The TRP will be readjusted every 3 weeks.

The same cuff used in the TRP evaluation will be inflated in the proximal end of the thigh immediately before the exercises (squatting in the hack machine and extension of the leg) and will remain inflated during the interval rest between sets. The cuff will be removed during the 2-min interval between exercises. Fluctuations in prescribed pressure (60% of TRP) will be monitored and regulated by the therapist [18]. The number of repetitions completed in each series will be monitored to check whether the total proposed volume was reached. The total duration of the BFR will be about 5 min per exercise.

The load during the squatting exercises on the hack machine and leg extension will be 10% of the estimated 1-RM [8] with 1 × 30 and 3 × 15 repetitions to be performed with a 30-s interval between sets [14, 15, 18, 20]. The total volume (load × repetitions × series) for each exercise per session will be estimated 1-RM × 0.1 × 75 = estimated 1-RM × 7.5 kg.

#### High-intensity resistance exercise

The HIRE group will perform 3 × 8 repetitions with 60% 1-RM for squatting on the hack machine and leg extension exercises [8] with an interval of 30 s between repetitions. Total volume (load × repetitions × series) for each exercise per session will be 1-RM estimated × 0.6 × 24 = 1-RM estimated × 14.4 kg. In the HIRE group, a BFR placebo with the same cuff used in the BFR exercise group but inflated with a minimum pressure (10 mm Hg) will be applied. This BFR level will not affect the number of repetitions per session [20].

### Primary outcome

The primary outcome is knee pain at rest and during the 30-s chair stand test and will be measured by using the VAS from 0 to 100 mm, where “0 mm” means no pain and “100 mm” means maximum pain already experienced.

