### Sample size estimates

It is estimated that a sample size of 32 patients per group would be necessary to test our research hypothesis on the primary outcome (knee pain). The parameters utilized to sample size calculation included an intergroup variability (σ) in the VAS gain of 21% for both groups [44]; a non-inferiority limit (d) of 14%, which is less than the minimum clinically perceptible difference, usually considered to be 15% for the VAS [45]; a type-I error of 5% (α =0.05); a power of 80% (β=0.20) and a dropout rate of 15%.

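### The primary outcome is defined as two VAS pain scores, but the sample size covers one test of one score and no rule says which score decides

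*Protocol article*

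**What the plan says.** The Primary outcome section reads: "The primary outcome is knee pain at rest and during the 30-s chair stand test", measured on a VAS from 0 to 100 mm. Pain at rest and pain during a loaded task are two conditions and give two readings per visit.

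Elsewhere the outcome is treated as one variable. The abstract says: "The primary outcome will be the knee pain measured after 12 weeks of treatment". The Sample size estimates section says that "a sample size of 32 patients per group would be necessary to test our research hypothesis on the primary outcome (knee pain"), and lists one value for each input: "an intergroup variability (σ) in the VAS gain of 21% for both groups"; "a non-inferiority limit (d) of 14"%; "a type-I error of 5% (α =0.05"); and "a power of 80% (β=0.20) and a dropout rate of 15"%. None of these is tied to the rest score or the chair-stand score.

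Table 1 has a single VAS row for the outcome visits (baseline, 72 h post treatment, week 24). The Statistical analyses section gives a general between-group test and a 95% confidence interval. It does not mention two primary scores.

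**The concern.** The two scores can disagree: the BFR arm could meet the margin on one and miss it on the other. As written, nothing settles what the trial would then conclude, so the deciding score could be picked after the results are known. In a non-inferiority comparison this is the central claim of the trial.

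The gap also affects the design figures. One test of one score has a definite error rate and power. Two scores without a rule do not, so the 5% and 80% in the sample size section are not secured by the outcome as defined. The follow-up pain outcome inherits the ambiguity, because it is defined by reference back to the primary outcome.

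**Working it through.** **Inputs.** From Sample size estimates: SD 21, margin 14, type I error 5% (sidedness not stated), power 80%, dropout 15%, 32 per group. Assumed: a true difference of zero for power; the same SD and margin for both scores; a bivariate normal distribution. The correlation between the scores is not in the article, so 0 to 0.9 is shown.

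**Step 1. Reproduce the stated size.** For one non-inferiority test of one mean, n per group = 2 × [SD × (z for alpha + z for power) / margin]².

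- One-sided 5%: 2 × [21 × (1.645 + 0.842) / 14]² = 27.8, so 28 evaluable. With dropout, 27.82 × 1.15 = 31.99, or 32; dividing by 0.85 instead gives 32.7, or 33. This reproduces the stated 32.
- One-sided 2.5%: 2 × [21 × (1.960 + 0.842) / 14]² = 35.3, so 36 evaluable and 42 to 43 per group with dropout. This does not reproduce 32.

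The stated size is therefore that of one test, on one score, at one-sided 5%.

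**Step 2. Single-score power with 28 evaluable per group.** Power = Φ(14 / [21 × √(2/28)] − z for alpha), and 14 / [21 × √(2/28)] = 2.494.

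- One-sided 5%: Φ(2.494 − 1.645) = 0.802.
- One-sided 2.5%: Φ(2.494 − 1.960) = 0.703.

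**Step 3. Two scores at one-sided 5% each.**

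- Either suffices: error = 1 − P(neither test rejects), with both true differences at the margin. At correlation 0 this is 1 − 0.95² = 0.0975.
- Both required: the error stays at or below 5%, and power = P(both tests reject). At correlation 0 this is 0.802², about 0.64.

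| Correlation | Error if either suffices | Power if both required (28 evaluable) | Evaluable per group for 80% joint power |
|---|---|---|---|
| 0 | 9.75% | 64% | 38 |
| 0.5 | 8.8% | 69% | 36 |
| 0.8 | 7.5% | 73% | 34 |
| 0.9 | 6.8% | 75% | 32 |

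With dropout (dividing by 0.85), the last column becomes 45, 43, 40 and 38 per group.

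**Step 4. Two scores judged on a 95% interval (one-sided 2.5% each).** The either-suffices error is 4.9%, 4.5%, 4.2% and 3.5% at correlations 0, 0.5, 0.7 and 0.9, never above 5%. Single-score power is about 70% (step 2).

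**The case against.** The strongest reply is that the article leaves the rule open and does not fix a wrong one. A reader might infer that either the error rate or the power must be wrong. The documents do not support that: one named score, a fixed testing order or a pre-specified average would each keep a single 5% test. For an average, the SD of 21 would need its own support. What is shown is that the figures are undetermined. This stands, and the ranges above apply only to the two readings named.

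The error inflation is also conditional. One-sided 5% is inferred from the stated size, while the only interval the article mentions is a 95% one. On that interval, either-score power at 28 evaluable is 2 × single-score power − both-score power. At correlation 0 this is 2 × 0.703 − 0.495 = 91%, and at 0.7 it is 2 × 0.703 − 0.595 = 81%. So 5% and 80% could both hold under an either-suffices rule up to a correlation of about 0.7. This stands as arithmetic. However, the article states no such rule, does not link the interval to the margin, and was not sized at that level.

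Third, decision rules are often left to an analysis plan or full protocol not shown here. That excuses missing testing detail. It does not excuse an outcome section that defines two scores beside a sample size section that counts one.

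Other inferences to avoid:

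- That rest pain would sit near zero and so favour a non-inferiority claim. No baseline VAS values are given. There is no VAS entry minimum, but a Lequesne score of 5 to 13 is required, so the claim cannot be checked.
- That the total of 40 patients worsens this point. Its conflict with 32 per group is a separate matter.
- That the time point is open. The abstract sets 12 weeks, Table 1 sets 72 h post treatment, and the later VAS is secondary.

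**Conclusion.** The point holds as an inconsistency within the article: two VAS scores are presented as one primary outcome, the trial is sized for one score, and no passage says which score decides or how they combine.

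At the one-sided 5% that reproduces 32 per group, the type I error is about 9.75% down to 6.8% if either score may count, and power is about 64% up to 75% instead of 80% if both must succeed, as the correlation goes from 0 to 0.9. On a 95% interval the either-score error stays below 5%, at the price of single-score power of about 70%.

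These figures rest on equal SD and margin for both scores, 28 evaluable per group, and a correlation the article does not give. Both effects shrink as the correlation approaches 1.

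**What to change.** In the Primary outcome section, name one of the two scores, at the 72 h post-treatment visit already scheduled, as the sole primary outcome and make the other the first secondary. In Sample size estimates, state which score the SD of 21 and the margin of 14 refer to.

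If both scores are to stay primary, declare them co-primary, with both required to meet the margin and no alpha adjustment. Then restate the power as about 64% to 75% at 28 evaluable per group. Holding 80% joint power would need the larger numbers in the table above.

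The change should be made before unblinded outcome data are seen, and any registry wording brought into line. Both scores are still collected, so the cost is a few sentences. The downside is that one score loses primary status or, with co-primaries, that a lower power is stated.
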